## Abstract

**Objectives:**

The aim of this trial is to evaluate the antiviral efficacy, clinical efficacy, and safety of nelfinavir in patients with asymptomatic and mild COVID-19.

**Trial design:**

The study is designed as a multicenter, open-label, blinded outcome assessment, parallel group, investigator-initiated, exploratory, randomized (1:1 ratio) controlled clinical trial.

**Participants:**

Asymptomatic and mild COVID-19 patients will be enrolled in 10 university and teaching hospitals in Japan. The inclusion and exclusion criteria are as follows:

Inclusion criteria:
Japanese male or female patients aged ≥ 20 yearsSARS-CoV-2 detected from a respiratory tract specimen (e.g., nasopharyngeal swab or saliva) using PCR, LAMP, or an antigen test within 3 days before obtaining the informed consentProvide informed consent

Exclusion criteria:
Symptoms developed ≥ 8 days prior to enrolmentSpO_2_ < 96 % (room air)Any of the following screening criteria:ALT or AST ≥ 5 × upper limit of the reference rangeChild-Pugh class B or CSerum creatinine ≥ 2 × upper limit of the reference range and creatinine clearance < 30 mL/min(4)Poorly controlled diabetes (random blood glucose ≥ 200 mg/dL or HbA1c ≥ 7.0%, despite treatment)(5)Unsuitable serious complications based on the assessment of either the principal investigator or the sub-investigator(6)Hemophiliac or patients with a marked hemorrhagic tendency(7)Severe diarrhea(8)Hypersensitivity to the investigational drug(9)Breastfeeding or pregnancy(10)With childbearing potential and rejecting contraceptive methods during the study period from the initial administration of the investigational drug(11)Receiving rifampicin within the previous 2 weeks(12)Participated in other clinical trials and received drugs within the previous 12 weeks(13)Undergoing treatment for HIV infection(14)History of SARS-CoV-2 vaccination or wishes to be vaccinated against SARS-CoV-2(15)Deemed inappropriate (for miscellaneous reasons) based on the assessment of either the principal investigator or the sub-investigator

**Intervention and comparator:**

Patients who meet the inclusion criteria and do not meet any of the exclusion criteria will be randomized to either the nelfinavir group or the symptomatic treatment group.

The nelfinavir group will be administered 750 mg of nelfinavir orally, three times daily for 14 days (treatment period). However, if a participant tests negative on two consecutive PCR tests of saliva samples, administration of the investigational drug for that participant can be discontinued at the discretion of the investigators.

The symptomatic treatment group will not be administered the investigational drug, but all other study procedures and conditions will be the same for both groups for the duration of the treatment period. After the treatment period of 14 days, each group will be followed up for 14 days (observational period).

**Main outcomes:**

The primary endpoint is the time to negative conversion of SARS-CoV-2. During the study period from Day 1 to Day 28, two consecutive negative PCR results of saliva samples will be considered as the negative conversion of the virus.

The secondary efficacy endpoints are as follows:

For patients with both asymptomatic and mild disease: area under the curve of viral load, half decay period of viral load, body temperature at each time point, all-cause mortality, incidence rate of pneumonia, percentage of patients with newly developed pneumonia, rate of oxygen administration, and the percentage of patients who require oxygen administration.

For asymptomatic patients: incidence of symptomatic COVID-19, incidence of fever (≥ 37.0 °C for two consecutive days), incidence of cough

For patients with mild disease: incidence of defervescence (< 37.0 °C), incidence of recovery from clinical symptoms, incidence of improvement of each symptom

The secondary safety endpoints are adverse events and clinical examinations.

**Randomization:**

Patients will be randomized to either the nelfinavir group or the symptomatic treatment group using the electric data capture system (1:1 ratio, dynamic allocation based on severity [asymptomatic], and age [< 60 years]).

**Blinding (masking):**

Only the assessors of the primary outcome will be blinded (blinded outcome assessment).

**Numbers to be randomized (sample size):**

The sample size was determined based on our power analysis to reject the null hypothesis, S (t | z =1) = S (t | z = 0) where S is a survival function, t is time to negative conversion, and z denotes randomization group, by the log-rank test with a two-sided p value of 0.05. We estimated viral dynamic parameters by fitting a nonlinear mixed-effects model to reported viral load data, and simulated our primary endpoint from viral-load time-courses that were realized from sets of viral dynamics parameters sampled from the estimated probability distribution of the parameters (sample size: 2000; 1000 each for randomization group). From this estimation of the hazard ratio between the randomization groups for the event of negative conversion using this simulation dataset, the required number of events for rejecting our null hypothesis with a power of 0.80 felled 97.345 by plugging the estimated hazard ratio, 1.79, in Freedman’s equation. Therefore, we decided the required number of randomizations to be 120 after consideration of the frequency of censoring and the anticipated rate of withdrawal caused by factors such as withdrawal of consent.

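### The stated primary test uses randomisation group alone; adjusting for Day 1 viral load and the allocation factors would probably add power at no extra patients

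*Protocol article*

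**What the plan says.** The primary endpoint is time to viral clearance in saliva: "During the study period from Day 1 to Day 28, two consecutive negative PCR results of saliva samples" define the event (Main outcomes). The only comparison stated for it is in the section Numbers to be randomized (sample size). The null hypothesis equates the two survival functions, "where S is a survival function, t is time to negative conversion, and z denotes randomization group", and is to be rejected "by the log-rank test with a two-sided p value of 0.05". No covariate or stratum enters.

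The same section says that the endpoint was simulated from viral-load curves whose parameters vary between patients. The resulting group-level effect was used "by plugging the estimated hazard ratio, 1.79, in Freedman’s equation", so that "the required number of events for rejecting our null hypothesis with a power of 0.80 felled 97.345", and "we decided the required number of randomizations to be 120 after consideration of the frequency of censoring and the anticipated rate of withdrawal".

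The Randomization section gives "1:1 ratio, dynamic allocation based on severity [asymptomatic], and age [< 60 years" as the scheme; viral load is not a balancing factor. Main outcomes lists "area under the curve of viral load, half decay period of viral load" among the secondary endpoints, so viral load is measured quantitatively. A Day 1 value is implied, though not named.

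**The concern.** In a viral-dynamics model, the time at which load falls below detection depends on where the curve stands at entry and how fast it falls. By the planning model's own logic, starting load should therefore predict the primary endpoint.

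Starting load is also likely to vary. The exclusion criteria let symptomatic patients enter across about a week of illness. Asymptomatic patients need only a positive test within the 3 days before consent, with no limit on time since infection.

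A comparison that ignores a prognostic baseline variable has less power than one that uses it. Severity and age were thought important enough to steer allocation, yet they too are absent from the stated test. What is at stake is power that could be had from data already being collected.

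**Working it through.** **1. Reproduce the plan's event count.** Inputs from the sample-size section: HR 1.79, two-sided 0.05, power 0.80, Freedman's formula; 1:1 allocation.

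Events = (1.960 + 0.842)² × ((1 + HR)/(1 − HR))² = 7.849 × (2.79/0.79)² = 97.90.

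The article gives 97.345. An unrounded HR of about 1.793 gives 97.37, so the gap is rounding of the HR and the figure reproduces. It requires 97.345/120 = 81% of randomised patients to have an event.

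**2. Power of the stated test at 98 events.**
- Freedman: Φ(√98 × 0.79/2.79 − 1.960) = Φ(0.843) = 0.80.
- Schoenfeld: Φ(√98 × ln(1.79)/2 − 1.960) = Φ(0.922) = 0.82.

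The unadjusted test meets its target. The 1.79 was estimated between groups of simulated patients who differ in their viral dynamics, so dilution from that variation is already in it.

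**3. What adjustment for starting load could add.** The article gives no figure for prognostic strength, so it is varied here as an assumption. The simulation used 60 patients per arm, 28 days, 5% withdrawal, about 98 events, Weibull times (shape 1.5), a standardised baseline log load and 4,000 replicates per row. The treatment effect was recalibrated in each row to hold the unadjusted HR near 1.79. Both analyses are Cox models tested at |z| > 1.96.

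| Assumed HR per SD of log load | Conditional treatment HR | Power unadjusted | Power adjusted | Gain (points) |
|---|---|---|---|---|
| 1.00 (not prognostic) | 1.79 | 0.81 | 0.81 | 0 |
| 0.74 | 1.85 | 0.82 | 0.86 | 4 |
| 0.61 | 1.95 | 0.81 | 0.91 | 9 |
| 0.50 | 2.10 | 0.82 | 0.96 | 14 |
| 0.37 | 2.36 | 0.81 | 0.99 | 17 |

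**4. Does the gain survive less ideal conditions?** A second simulation was also calibrated to an unadjusted HR of 1.79. It added measurement noise to Day 1 load, sampled every 2 days, and used a covariate-adjusted score test. The gain was about 4 to 11 points, with two-sided rejection under the null of at most 0.054. The noise level and sampling interval are assumptions.

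No gain was calculated for severity and age, because the article gives nothing from which to judge their strength.

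**The case against.** **The article is a summary.** It has no analysis section, and it says that the full protocol is attached separately. Covariates may be specified there or in the SAP. This stands as a condition on the fix. It does not remove the point, because the article does state a primary hypothesis and a test, and both use group alone. The same argument does dispose of any criticism of the viral-load AUC analysis: the article names that endpoint but states no method for it.

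**A reader might infer that the trial is underpowered.** The documents do not support this. The event count reproduces and power is 0.80 to 0.82 at 98 events. A simple model with time equal to the excess of baseline load over the detection limit, divided by decay rate, gives unadjusted power of only 0.68 to 0.76. Those figures do not match the plan's own HR and event count and are not used here.

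**A reader might infer that chance imbalance in viral load invalidates the comparison.** With 60 per arm, the difference in mean baseline load has a standard error of √(2/60) = 0.18 SD, so differences up to about ±0.36 SD are unremarkable and can shift one trial's estimate. Under randomisation, the log-rank test's error rate already allows for this.

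**The adjusted test may be liberal.** In the simple model above, an adjusted Wald test rejected at 0.024 to 0.039 one-sided under the null, against a nominal 0.025. That stands against a Wald test and is why a score or re-randomisation test is proposed. The score-test simulation still showed a gain.

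**The covariate has practical gaps.** Entry may rest on a PCR, LAMP or antigen result from any respiratory specimen, so Day 1 saliva may be below detection. The adjusted HR is also a different quantity from the 1.79 used in planning. Both points stand, and the fix has to cover them.

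**The trial is described as exploratory, and an unadjusted log-rank test is a legitimate choice.** Agreed. The recommendation rests on efficiency only.

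**Conclusion.** The point holds as a missed efficiency. The stated primary test is valid and adequately powered on its own terms, but it uses neither the two allocation factors nor the Day 1 viral load that the planning model ties to the endpoint.

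The gain from adjusting for load is none if load is not prognostic. It is roughly 4 to 17 points of power at 120 patients if the hazard ratio per SD of log load lies between 0.74 and 0.37, and about 4 to 11 points in the simulation with noisy load, spaced sampling and a score test. That starting load is prognostic follows from the structure of the planning model; how strongly is an assumption. The conclusion also depends on the full protocol and SAP not already specifying adjustment.

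**What to change.** First check the full protocol and SAP. If an adjusted primary analysis is already specified there, say so in the sample-size text and stop. Otherwise, before analysts see outcome data:

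- Make the primary test a covariate-adjusted score test (or a re-randomisation test that follows the dynamic allocation), with severity, age group and pre-dose Day 1 log10 saliva viral load.
- Set Day 1 values below detection to the detection limit.
- Report the adjusted hazard ratio as conditional on these covariates. It is expected to lie further from 1 than the group-level 1.79 (1.85 to 2.10 in the three middle rows of the table).
- Keep the unadjusted log-rank test as a sensitivity analysis.

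The sample size and event target need no change. The cost is analysis wording, plus confirmation that the Day 1 saliva sample is quantified and taken before the first dose; no patient or visit is added.

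### Allocation balances severity and age, but the only test named for the primary endpoint compares groups alone; stratifying it is a nearly free safeguard if those factors are strongly prognostic

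*Protocol article*

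**What the plan says.** The Randomization section describes the allocation as "1:1 ratio, dynamic allocation based on severity [asymptomatic], and age [< 60 years". It gives no reason for choosing these two factors.

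The sample-size section opens with "The sample size was determined based on our power analysis to reject the null hypothesis". The null hypothesis is equality of the survival functions for time to negative conversion in the two groups, where "z denotes randomization group", and it is to be rejected "by the log-rank test with a two-sided p value of 0.05". Neither severity nor age enters the hypothesis or the test. The event count follows from "plugging the estimated hazard ratio, 1.79, in Freedman’s equation", and the section concludes that "we decided the required number of randomizations to be 120". The article has no separate section on the primary analysis, so this paragraph is its only inferential statement about the primary endpoint.

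**The concern.** Factors that steer the allocation are normally carried into the analysis. If severity and age affect how fast saliva PCR turns negative, leaving them out of a log-rank test has two effects. First, allocation has removed chance imbalance on these factors, but the unstratified variance still allows for it, so the test tends to be conservative. Second, mixing patients with different clearance rates pulls the overall hazard ratio towards 1 relative to the ratio within strata. Both effects reduce power compared with a stratified test on the same patients. At stake is efficiency in a trial of 120 patients, not the soundness of a positive result.

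**Working it through.** **1. The plan's own figure.** Inputs from the sample-size section: hazard ratio 1.79, two-sided alpha 0.05, power 0.80; 1:1 allocation from the Randomization section. Freedman's formula:

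events = (z₀.₉₇₅ + z₀.₈₀)² × ((1 + HR)/(1 − HR))² = (1.960 + 0.842)² × (2.79/0.79)² ≈ 7.849 × 12.473 ≈ 97.9

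The article gives the result "with a power of 0.80 felled 97.345". The gap of about 0.55 events is explained by rounding of the hazard ratio: 1.7925 gives 97.45 and 1.795 gives 97.01, so about 1.793 yields the stated figure. The figure reproduces. As a share of those randomized, 97.345/120 = 81% would have an event. The formula has no term for strata, so stratifying the test changes neither the event count nor the 120.

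**2. Unstratified against stratified log-rank.** The size of any loss depends on how prognostic the factors are, which the article does not give, so a range is needed. Assumptions: 120 patients, exponential times censored at Day 28, about 97 events, 30% asymptomatic, 25% aged 60 or over, allocation balanced within the four strata, within-stratum treatment hazard ratio 1.79, two-sided 0.05, and 3000 simulated trials per setting. Monte Carlo error is about 0.7 points on power and 0.4 on type I error. Factor hazard ratios are asymptomatic versus mild / 60 or over versus under 60.

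| Assumed factor HRs | Power, unstratified | Power, stratified | Gain from stratifying (points) | Type I error, unstratified | Type I error, stratified |
|---|---|---|---|---|---|
| 1 / 1 | 81.0% | 80.0% | −1.0 | 5.8% | 5.6% |
| 1.25 / 0.8 | 81.3% | 81.2% | −0.1 | 4.8% | 4.8% |
| 1.5 / 0.67 | 80.3% | 80.8% | +0.5 | 4.6% | 5.3% |
| 2 / 0.5 | 73.7% | 79.8% | +6.1 | 3.7% | 5.1% |
| 3 / 0.33 | 65.8% | 80.9% | +15.1 | 2.2% | 5.0% |

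**3. The same comparison under minimization.** The article says only that allocation is dynamic; balance within every cell is an assumption of step 2. A second simulation used minimization instead (1000 trials per setting, about 97 to 101 events, within-stratum hazard ratio 1.79; Monte Carlo error about √(0.8 × 0.2/1000) = 1.3 points).

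| Assumed factor HRs | Power, unstratified | Power, stratified | Gain from stratifying (points) |
|---|---|---|---|
| 1 / 1 | 81.5% | 79.8% | −1.7 |
| 1.5 / 0.67 | 82.5% | 82.4% | −0.1 |
| 2 / 0.5 | 75.3% | 78.5% | +3.2 |
| 3 / 0.5 | 69.9% | 78.4% | +8.5 |

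**4. Reading the two together.** With factors of no or moderate strength the tests are practically equivalent, and stratifying costs at most about 1 to 2 points. At 2/0.5 the unstratified test gives up about 3 to 6 points, and at 3/0.5 to 3/0.33 about 9 to 15. The unstratified test becomes conservative as the factors strengthen; its type I error never exceeds 5% beyond simulation error.

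**The case against.** The strongest objection is that the article does not state the primary analysis. The log-rank test appears in a paragraph about sample size, and sizing with a plain log-rank formula is usual even when the analysis is stratified. The article says that it condenses a full protocol, which is not at hand, and stratification is commonly settled there or in a SAP. This stands in part. A reader might infer that the sponsor has committed to an unstratified primary test, but the article never says so. What remains is that the paragraph goes beyond applying a formula: it writes out the null hypothesis by group alone and names the test, and nothing else in the article brings in the allocation factors.

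A reader might also infer that the trial falls short of its planned power of 0.80. The article does not support that. The ratio of 1.79 comes "From this estimation of the hazard ratio between the randomization groups for the event of negative conversion using this simulation dataset", with no stratification described. It may therefore already be a marginal ratio that includes the attenuation from differences between patients. The simulations set 1.79 within strata, so they compare the two tests with each other and do not re-estimate the trial's power.

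Third, no reason is given for the choice of factors and no prognostic strength is stated, so a loss of power cannot be asserted as fact. This stands: the loss is conditional and is negligible for weak to moderate factors.

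Finally, the unstratified test is valid, and the trial is described as exploratory. Both are true, and they make this an improvement in efficiency rather than the repair of an error.

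**Conclusion.** The point holds in a limited form. Taken at its word, the only test named for the primary endpoint ignores the two factors that govern allocation. Such a test is valid, but it can be conservative and less powerful than a stratified one. The size ranges from nothing to about 15 points of power and depends on assumed prognostic effects; a material gain from stratifying appears only when the factors are strongly prognostic, at about 2/0.5 and beyond. These figures also rest on the assumed exponential times, event fraction, stratum mix and form of balancing. The case for stratifying is its asymmetry: little to lose if the factors do not matter, several points to gain if they do.

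**What to change.** Before outcome data are analysed, specify the primary test as a log-rank test stratified by severity (asymptomatic or mild) and age (under 60, or 60 and over). Report the hazard ratio from a Cox model stratified by, or adjusted for, the same factors, and keep the unstratified log-rank test as a sensitivity analysis. State in advance that if a stratum is sparse, the Cox model adjusted for both factors will be used instead.

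The cost is a sentence or two of analysis wording, since both factors are already recorded for allocation. The possible price is the 1 to 2 points of power noted above. If the full protocol or SAP already stratifies or adjusts, it is enough to align the description of the test with it.

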**Trial Status:**

Protocol version 6.0 of February 12, 2021. Recruitment started on July 22, 2020 and is anticipated to be completed by March 31, 2022.

**Trial registration:**

This trial was registered in Japan Registry of Clinical Trials (jRCT) (jRCT2071200023) on 21 July 21, 2020.

**Full protocol:**

The full protocol is attached as an additional file, accessible from the Trials website (Additional file 1). In the interest in expediting dissemination of this material, the familiar formatting has been eliminated; this Letter serves as a summary of the key elements of the full protocol.

The study protocol has been reported in accordance with the Standard Protocol Items: Recommendations for Clinical Interventional Trials (SPIRIT) guidelines (Additional file 2).

**Supplementary Information:**

The online version contains supplementary material available at 10.1186/s13063-021-05282-w.

## Data Availability

The full study protocol is available in the supplementary materials and at https://jrct.niph.go.jp/en-latest-detail/jRCT2071200023. The data are not available because the trial is in progress. The data will be made available from the author on reasonable request once the trial has been completed. Please contact the corresponding author, Dr. [name] ([contact]).
